## Materials and methods

2

### RISE development and evaluation framework

2.1

Adaptation and evaluation of the RISE intervention will follow the ADAPT-ITT [122] framework, an eight-phase model guiding adaptation of evidence-based interventions for new populations and contexts (for more detail, see Table 1). Phases I-III, including literature review and needs assessment, selection of intervention components, and preliminary mapping of treatment targets and mechanisms, were completed prior to the current protocol and informed the intervention rationale described in the Introduction. Building on this foundation, Aim 1 will implement ADAPT-ITT Phases IV–VII through iterative adaptation procedures with SMW/TGD community members and mental and behavioral health providers working with SMW/TGD people, and Aim 2 will implement Phase VIII through pilot testing of the adapted intervention.

**Table 1 tbl1:** ADAPT-ITT model (Wingood et al., 2008) adaptation process.

Adaptation phase	Task	Study phase	Methods
1. Assessment	Who is the new target population and why is it at risk?	Completed	- Conducted a targeted review on hazardous drinking and posttraumatic stress among SMW/TGD populations to define mechanism targets, dosing, and telehealth delivery constraints
2. Decision	What evidence-based intervention is to be adapted?	Completed	- Reviewed literature and identified the need to adapt a brief, telehealth CBT-EW intervention
3. Administration	What in the original evidence-based intervention needs to be adapted and how?	Completed	- Specified core components (UP Modules 2–5 + 5-day EW) based on mechanism mapping - Predefined adaptation parameters by examining manuals, existing literature, and consulting with the research team
4. Production	How to produce and document adaptation to evidence-based intervention?	Aim 1, Step 1	- Develop Draft v0.1 of the RISE manual that preserves active ingredients and theoretical rationale - Create participant handouts, clinician check-in/safety scripts, and fidelity checklists
5. Topic experts	Who can help to adapt the evidence-based intervention?	Aim 1, Step 2	- Conduct semi-structured interviews with 10 mental/behavioral health providers serving SMW/TGD people reporting hazardous drinking and posttraumatic stress symptoms - Conduct focus groups with 20 SMW/TGD community members who report hazardous drinking and posttraumatic stress symptoms; piloting brief elements (e.g., mindfulness exercise, EW prompt) to evaluate clarity, tone, comprehension, burden, cultural responsiveness, feasibility, and perceived barriers
6. Integration	What is going to be included in the adapted evidence-based intervention to pilot?	Aim 1, Step 3	- Analyze qualitative data using a rapid, framework-guided thematic analysis approach - A preliminary codebook—organized around mechanism fit, cultural fit, feasibility, and safety— will be developed, double-coded on an initial subset, and refined to consensus - Maintain an audit trail and discrepancy log - Build a change matrix (issue → evidence → revision → priority/feasibility rating) - Incorporate revisions until no new high-priority modifications emerge - Document adaptation rationale linking each change to community member and provider input and the mechanism framework - Produce Manual v1.0 (instructions, scripts, timing, participant workbook/handouts, fidelity and competence checklists, clinical protocol for conducting risk assessments) - Finalize trial flow (screening, randomization, assessment schedule, data capture, adverse-event monitoring) and implement data quality checks (attention/fraud flags for online components)
7. Training	Who needs to be trained and how?	Aim 2, Step 1	- Establish procedures and standardized training package for RISE interventionists (telehealth orientation, competency goals, didactics on mechanisms and cultural adaptations for SMW/TGD participants, module-specific demonstrations, standardized role-plays, safety planning), supervision plan (format, frequency, case review cadence), fidelity monitoring (checklists, rating rubrics, sampling plan), and assessor training for clinician-delivered measures
8. Testing	Did adaptation work?	Aim 2, Step 2	- Randomize SMW/TGD participants with hazardous drinking and posttraumatic stress symptoms to RISE or waitlist control; deliver the intervention; collect feasibility/acceptability metrics and preliminary alcohol and traumatic-stress outcomes to inform refinement and power calculations for a definitive trial

***Note.*** SMW/TGD = sexual minority cisgender women, transgender women, transgender men, nonbinary people, and gender-diverse individuals; CBT = cognitive behavioral therapy; RISE = **R**ecovery through **I**nhibitory learning, **S**elf-**E**fficacy promoting, problem-solving, and community building.

#### Trial design

2.1.1

To address Aim 2, we will conduct a pilot randomized controlled trial using a parallel, 1:1 unstratified allocation design comparing immediate treatment receipt with a 6-week waitlist control condition (see Fig. 1). Consistent with the pilot nature of the study, treatment outcome findings will be interpreted as preliminary estimates intended to inform feasibility, acceptability, and future efficacy testing. Outcome data will be collected through virtual clinician-administered interviews and online self-report assessments. Participants randomized to immediate treatment will complete assessments at baseline, post-treatment (following completion of UP modules and EW sessions), and 1-week follow-up. Participants randomized to the waitlist condition will complete assessments at baseline, post-waitlist (i.e., second baseline/prior to treatment initiation), post-treatment, and 1-week follow-up (see Fig. 1).

**Fig. 1 fig1:**
[figure not shown]
Aim 2 participant flow diagram. Description of the image: The figure depicts study procedures for Aim 2, including eligibility screening, baseline assessment, allocation to condition, RISE intervention/waitlist control, post-treatment assessment, and exit interview. Anticipated schedule, compensation, and measures assessed at each time point are detailed.

#### Participants

2.1.2

##### Aim 1: adaptation phase participants

2.1.2.1

Aim 1 will enroll 20 SMW/TGD community members and 10 mental or behavioral health providers. Eligible community members will: identify as sexual minority cisgender women, transgender women, transgender men, nonbinary people, or gender diverse people (e.g., genderqueer, agender); be ≥ 18 years; speak English; have reliable internet access and access to a smartphone, tablet, or computer; screen positive for hazardous drinking (Alcohol Use Disorders Identification Test-Consumption [AUDIT-C] ≥3 [123]; endorse at least minimal motivation to reduce drinking (Readiness Ruler ≥4) [124]; report ≥1 potentially traumatic event on the Life Events Checklist [125]; and meet at least subthreshold posttraumatic stress disorder criteria on the PTSD Checklist-5 (PCL-5) [126]. Consistent with PTSD assessment recommendations [127], subthreshold PTSD eligibility will require endorsement of ≥1 Criterion B (re-experiencing), C (avoidance), D (negative cognitions or mood), and E symptom (exaggerated arousal). The AUDIT-C cutoff of ≥3 was selected to identify hazardous drinking while maximizing sensitivity to clinically meaningful alcohol-related risk among SMW/TGD populations, recognizing that alcohol-related risk in these communities may occur at comparatively lower levels of alcohol consumption [56]. Cisgender sexual minority men, cisgender heterosexual men, and transgender or gender diverse individuals who identify as heterosexual will not be included given that the intervention is designed to address co-occurring hazardous drinking, posttraumatic stress symptoms, and stigma facing sexual minority cisgender women, transgender women, transgender men, nonbinary people, or gender diverse people. Community members will be required to reside in Rhode Island, Massachusetts, or Connecticut with intent to remain in the area for at least five months to support completion of study activities, including enrollment, intervention participation, post-treatment assessments, and follow-up procedures. This criterion was selected to minimize attrition due to relocation-related issues.

Providers will be eligible if they are ≥18 years old, speak English, currently provide mental or behavioral health services to SMW/TGD clients reporting hazardous drinking and posttraumatic stress symptoms, and either reside in or provide services within Rhode Island, Massachusetts, or Connecticut to ensure familiarity with the regional service environment, referral landscape, and local clinical, sociocultural, and service-delivery contexts relevant to intervention adaptation. For Aim 1, the only exclusion for providers and community members is failure to meet eligibility criteria.

##### Aim 2: pilot randomized trial participants

2.1.2.2

Aim 2 will enroll 60 SMW/TGD community members randomized 1:1 (unstratified) to immediate RISE or a 6-week waitlist condition. Inclusion criteria will mirror Aim 1 community eligibility criteria. Additional Aim 2 exclusions are intended to reduce treatment contamination and ensure participant safety during this early-stage pilot. Exclusions include: current mental health treatment ≥1 day/month; CBT within the past three months (participants remain eligible to seek care after enrollment); current alcohol or drug use disorder treatment other than mutual self-help (e.g., Alcoholics Anonymous); current PTSD/trauma-focused treatment; need for alcohol detoxification (adapted self-report Clinical Institute Withdrawal Assessment for Alcohol-Revised [CIWA-Ar] ≥15); active psychosis (Revised Behavior and Symptom Identification Scale [BASIS-R] psychosis subscale ≥1); active mania (positive Altman Self-Rating Mania Scale [ASRM] screen); active suicidality (Suicidal Ideation Attributes Scale [SIDAS] ≥22); or legal mandate to attend treatment. Across both aims, community members and providers will be excluded if they fail attention checks or display fraudulent or bot-like responses [128].

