##### Aim 1 procedures

2.1.3.2

After eligibility confirmation through the electronic screening survey and synchronous virtual screening, Aim 1 participants will complete a brief (about 10-min) REDCap survey assessing sociodemographic characteristics and relevant treatment experiences (e.g., receiving or providing care related to hazardous drinking, posttraumatic stress, and SMW/TGD populations).

Following survey completion, providers will participate in an individual semi-structured virtual interview examining their experiences delivering treatment to SMW/TGD individuals with hazardous drinking and posttraumatic stress symptoms, perceived treatment gaps, and recommendations for intervention adaptation. Community members will participate in either an individual interview or focus group, according to participant preference, exploring treatment goals, prior treatment experiences, perceived barriers and facilitators to care, and feedback on intervention content and delivery.

Both providers and community members will pilot brief elements of RISE (e.g., psychoeducation excerpts, mindfulness exercise) and provide feedback regarding instructions, clarity, tone, comprehension, burden, cultural responsiveness, feasibility, safety, and perceived fit. Feedback will be synthesized using an adaptation matrix to identify recommended modifications, areas of convergence or divergence across participant groups, and proposed refinements to the RISE manual and participant workbook. Intervention components perceived as unacceptable, unsafe, confusing, excessively burdensome, or insufficiently aligned with treatment targets may be revised, replaced, or removed as appropriate. Proposed adaptations will be evaluated for cultural responsiveness, mechanism alignment, feasibility, and participant safety prior to finalization of intervention materials for Aim 2 pilot testing.

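### The Aim 2 exclusions do not cover prior Aim 1 participation, so people who helped adapt RISE can be randomised in the pilot that judges its acceptability

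*Protocol article*

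**What the plan says.** Aim 1 (section 2.1.2.1): "Aim 1 will enroll 20 SMW/TGD community members and 10 mental or behavioral health providers". Section 2.1.2.1 also states: "For Aim 1, the only exclusion for providers and community members is failure to meet eligibility criteria". Attention and fraud checks, given in section 2.1.2.2, apply to both aims.

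Aim 2 (section 2.1.2.2): "Aim 2 will enroll 60 SMW/TGD community members randomized 1:1 (unstratified) to immediate RISE or a 6-week waitlist condition". On who may enter: "Inclusion criteria will mirror Aim 1 community eligibility criteria". On the purpose of the further exclusions: "Additional Aim 2 exclusions are intended to reduce treatment contamination and ensure participant safety during this early-stage pilot". The list that follows covers current mental health, substance use or trauma treatment, recent CBT, need for detoxification, psychosis, mania, suicidality and legal mandate. Several items carry a named instrument and cut-off. Prior Aim 1 participation is not among them and is not mentioned as a bar elsewhere in the article.

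What Aim 1 members do (section 2.1.3.2): "Both providers and community members will pilot brief elements of RISE (e.g., psychoeducation excerpts, mindfulness exercise". Table 1, phase 5, describes the community focus groups as "piloting brief elements (e.g., mindfulness exercise, EW prompt". Under sections 2.1.3.2 and 2.1.3.6 their feedback goes into an adaptation matrix that guides changes to the manual and workbook.

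Section 2.1.3.1 gives one set of recruitment channels for the study. It ends Aim 1 participation after the interview or focus group, projects the end of Aim 1 recruitment for June 2026, and expects Aim 2 recruitment to start in August 2026.

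**The concern.** The article gives a contamination purpose for its exclusions and bars recent CBT, yet as written it admits people who have already tried parts of RISE and helped to shape it. The inclusion criteria, the three-state area and the recruitment channels are shared, and the gap between the two recruitment periods is about two months.

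Section 2.1.4 says that the pilot exists mainly to estimate feasibility and acceptability parameters for a later definitive trial. Four of these outputs could be affected:

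- **Acceptability.** Table 1, phase 8, asks whether the adaptation worked. If people whose advice produced the adaptation help to answer that, the answer is partly circular. The 20 exit interviews could draw on them too.
- **Completion and retention.** People who come back to the same team for a second study are plausibly more engaged than new recruits.
- **Recruitment yield and screening-to-enrolment ratio.** Aim 1 members have already passed the same inclusion criteria and are known to the team, so they convert more easily than a naive pool would.
- **Generalisation.** A definitive trial would recruit people with no part in the design.

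**Working it through.** **1. The plan's own figure.** Section 2.1.4 gives a target of 60 (30 per condition), incorporating about 20% attrition. No precision target is stated, so 60 cannot be derived; it can only be checked for consistency. 60 × 0.80 = 48 expected completers, and 48 / 0.80 = 60. The figure is coherent, and nothing below changes it.

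**2. Who is eligible.** Three rules side by side:

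| Rule | Effect on an Aim 1 community member |
|---|---|
| Aim 2 inclusion mirrors Aim 1 | Met once; must be met again at Aim 2 screening |
| Added Aim 2 treatment and safety exclusions | Removes those in care, with recent CBT, or with acute clinical findings |
| Exclusion for prior Aim 1 participation | None listed |

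The second row has force, because Aim 1 applied none of those exclusions. Whoever remains after it is eligible.

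**3. Largest overlap.** 20 Aim 1 community members / 60 Aim 2 places = 33.3%. The expected split at that maximum is 10 per arm. The true number lies between 0 and 20.

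**4. Shift in an acceptability proportion.** Shift = (k / 60) × d, where k is the number overlapping and d is the assumed difference between co-designers and others. The documents give no value for d; 10 to 30 points is an assumed range.

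| k | k / 60 | d = 10 | d = 20 | d = 30 |
|---|---|---|---|---|
| 5 | 8.3% | 0.8 | 1.7 | 2.5 |
| 10 | 16.7% | 1.7 | 3.3 | 5.0 |
| 20 | 33.3% | 3.3 | 6.7 | 10.0 |

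(Shifts in percentage points.)

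**5. Comparison with sampling error.** The 95% half-width at a proportion of 80% is 1.96 × √(0.8 × 0.2 / n). For n = 48 it is 11.3 points; for n = 60 it is 10.1 points. At modest overlap the shift is well inside this. It is systematic, though, so the confidence interval does not reflect it.

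**6. Effect on the between-arm contrast.** Aim 1 exposure comes before randomisation, so in expectation both arms carry the same share. Suppose brief exposure gave overlapping waitlist members 10% to 50% of the RISE effect (assumed). At full overlap the contrast would shrink by 0.333 × 0.10 = 3.3% to 0.333 × 0.50 = 16.7%. At k = 10 the range is 1.7% to 8.3%. Allocation is unstratified, so chance imbalance is possible: with 20 overlapping among 60 and 30 per arm, the hypergeometric probability of a 12:8 split or worse, in either direction, is 0.41.

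**The case against.** **The article is condensed.** The exclusion list opens with a verb that need not mean it is exhaustive, and a one-line re-enrolment rule could sit in the full protocol. No section invites Aim 1 members back. This shows that overlap is not planned, and that stands. It does not remove the point: the article sets out the exclusions at length, states a contamination purpose, and the rule as written admits these people.

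**The size is assumed.** The documents do not show that co-designers rate higher, nor by how much, and the article sets no acceptability threshold that a small shift could cross. This also stands. The range is illustrative and the direction is a judgement.

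A reader might also infer more than the documents support:

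- *That every Aim 1 member qualifies for Aim 2.* Only inclusion is shared. The added exclusions and fresh screening would remove some.
- *That the waitlist arm in particular is contaminated.* Exposure precedes randomisation and consists of brief elements; the plan itself accepts CBT that ended more than three months ago.
- *That Aim 1 members are meant to receive RISE,* because section 2.1.2.1 asks for residence "with intent to remain in the area for at least five months to support completion of study activities, including enrollment, intervention participation, post-treatment assessments". This reads more simply as shared criteria text. The waitlist path takes about 6 + 2 + 6 + 1 + 2 = 17 weeks, which fits within five months. For someone enrolled in November 2025, five months would end around April 2026, before Aim 2 opens.
- *That completers of the team's earlier expressive-writing pilot form a second overlapping group.* The article gives no size, date or region for that study, so this cannot be judged.

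**Conclusion.** The gap is real but limited. As written, Aim 1 community members who still meet the inclusion criteria and pass the added exclusions can be randomised in Aim 2. The main consequence is possible bias, probably upward, in the feasibility and acceptability estimates. Overlap cannot exceed 33% of places and is likely to be lower. On the assumed 10-to-30-point difference, the overall acceptability proportion would rise by between 0.8 points (5 overlapping) and 10 points (all 20). Only the extreme case approaches the sampling half-width of 10 to 11 points. Any effect on the waitlist contrast is secondary. The change is worth making because these estimates are what the pilot is for and the remedy is small.

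**What to change.** Before Aim 2 opens, add prior participation as an Aim 1 community member to the exclusions in section 2.1.2.2, and check it against study records at screening.

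If the team prefers to admit these people, record prior Aim 1 participation at baseline and report feasibility and acceptability with and without them.

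The cost of the exclusion is one sentence, a records check, and at most about 20 people lost from the recruitment pool. The alternative costs one baseline variable and one extra set of descriptive summaries. Acting before enrolment is simplest, because removing people after randomisation would conflict with the planned intention-to-treat analysis.

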#### Procedures

2.1.3

##### Recruitment and enrollment

2.1.3.1

Participants will be recruited through flyers, social media, and outreach to local organizations working with sexual and gender minority people, those with lived experience of trauma, or people who use substances, as well as violence-prevention organizations. Interested people will complete an electronic informed consent and eligibility survey, including contact information to schedule a virtual screening with a study team member to confirm eligibility.

**Aim 1 recruitment and enrollment.** Following eligibility confirmation, Aim 1 participants will receive instructions to complete a brief online survey and schedule an interview/focus group. Participation in Aim 1 will conclude following completion of an interview or focus group. Recruitment for Aim 1 began in November 2025 and is projected to conclude June 2026.

**Aim 2 recruitment and enrollment.** Aim 2 recruitment will occur following completion of Aim 1 adaptation activities. Recruitment for Aim 2 will begin after completion of Aim 1 and finalization of the adapted RISE manual and participant workbooks (anticipated August 2026). Following eligibility confirmation, Aim 2 participants will receive instructions to complete a baseline self-report assessment and schedule a virtual clinician-administered baseline assessment prior to randomization.

##### Aim 1 procedures

2.1.3.2

After eligibility confirmation through the electronic screening survey and synchronous virtual screening, Aim 1 participants will complete a brief (about 10-min) REDCap survey assessing sociodemographic characteristics and relevant treatment experiences (e.g., receiving or providing care related to hazardous drinking, posttraumatic stress, and SMW/TGD populations).

Following survey completion, providers will participate in an individual semi-structured virtual interview examining their experiences delivering treatment to SMW/TGD individuals with hazardous drinking and posttraumatic stress symptoms, perceived treatment gaps, and recommendations for intervention adaptation. Community members will participate in either an individual interview or focus group, according to participant preference, exploring treatment goals, prior treatment experiences, perceived barriers and facilitators to care, and feedback on intervention content and delivery.

Both providers and community members will pilot brief elements of RISE (e.g., psychoeducation excerpts, mindfulness exercise) and provide feedback regarding instructions, clarity, tone, comprehension, burden, cultural responsiveness, feasibility, safety, and perceived fit. Feedback will be synthesized using an adaptation matrix to identify recommended modifications, areas of convergence or divergence across participant groups, and proposed refinements to the RISE manual and participant workbook. Intervention components perceived as unacceptable, unsafe, confusing, excessively burdensome, or insufficiently aligned with treatment targets may be revised, replaced, or removed as appropriate. Proposed adaptations will be evaluated for cultural responsiveness, mechanism alignment, feasibility, and participant safety prior to finalization of intervention materials for Aim 2 pilot testing.

